## Adverse event (AE) and serious adverse event (SAE)

### Definition of adverse event (AE)

An Adverse event (AE) is defined as any untoward medical occurrence in a participant associated with the use of the study medication or occurring during the study, regardless of whether there is a causal relationship with the study medication or treatment process.

Endpoint events are not considered AEs unless, based on the investigator's best clinical judgment, considering the course, severity, or other characteristics of the event, it should be regarded as an exception in this clinical context.

Any AE, regardless of its severity or whether it is related to the study medication, should be recorded in the CRF from the time the participant signs the informed consent form until the end of the last scheduled visit as planned in the study protocol. The investigator should specifically describe the timing of the event, its severity, any actions taken regarding the study medication, symptomatic treatment provided, outcomes, and his/her judgment on whether the AE might have been caused by the study medication.

Laboratory test results, vital signs, or ECG abnormalities will be recorded as AEs if they are medically related to the study medication, such as when accompanied by clinical symptoms, necessitating symptomatic treatment, leading to discontinuation of the medication, or resulting in serious consequences.

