| Exclusion criteria | - Any other DSM-5 psychiatric disorder other than generalized anxiety disorder and social anxiety disorder diagnosed at present or lifetime; - Subjects with serious suicide ideation or attempts; - Subjects who have received treatments with adjunctive antidepressants and/or antipsychotic medications in the current depressive episode (small doses of benzodiazepines were permitted); - Subjects who have received non-drug treatments in past 6 months for more than 10 times, such as electroconvulsive therapy (ECT), repetitive transcranial magnetic stimulation (rTMS), and systemic psychotherapy; - DSM-5 alcohol or drug dependence; - History of head injury or loss of consciousness for more than 5 minutes; - Subjects with a history or current diagnose of major physical illness (such as thyroid disease, lupus erythematosus, diabetes, lung, liver and kidney damage, infection, major trauma and etc.); - Pregnant or breast-feeding; - Epilepsy, history of seizures or family history of epilepsy; - Receiving hormone therapy at present; - Transaminases (ALT or AST) 2 times or more above the upper limit of normal range; - QTc >= 430 msec (for males) or >= 450 msec (for females) in ECG; - Any subject with some other conditions that the researchers believe may affect the study results. |
| Study visits | Visits will be conducted at 0 weeks ± 2 days, 2 weeks ± 2 days, 4 weeks ± 2 days, and 8 weeks ± 2 days after enrollment in the trial. |
| Efficacy end points | Primary efficacy end points:   - MADRS response rate (defined as an improvement of ≥50% in the MADRS score from baseline) at week 4 and week 8. - MADRS remission rate (defined as a MADRS score of ≤10) at week 4 and week 8.   Secondary efficacy end points:   - Reduction rates in MADRS and Hamilton Anxiety Scale (HAMA) scores at each visit. - Change rates in each Clinical Global Impression (CGI) and Beck Suicidal Ideation Scale (BSI-CV) subscales scores at each visit. - Reduction rates in Pittsburgh Sleep Quality Index (PSQI), 16-item Quick Inventory of Depressive Symtomatology-Self-Report (QIDS-SR16), Generalized Anxiety Disorder 7-item Scale (GAD-7), and Snaith-Hamilton Pleasure Scale (SHAPS) scores at each visit. - Change rates in Sheehan Disability Scale (SDS) and Quality of Life Enjoyment Questionnaire - Short Form (Q-LES-Q-SF) scores at each visit. - Change rates in neurocognitive function test performance before and after treatment. |

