| Safety end points | - Adverse events rated by Treatment-Emergent Symptom Scale (TESS) - Incidence of adverse events |

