| Response rate | MADRS remission rate (defined as a MADRS score of ≤10) at week 4 and week 8. | To evaluate the clinical efficacy of perospirone as an adjunctive antidepressant treatment for MDD by assessing the proportion of patients with ≥50% reduction in MADRS scores at Week 4 and Week 8. |
| Remission rate | MADRS remission rate (defined as a MADRS score of ≤10) at week 4 and week 8. | To evaluate the clinical efficacy of perospirone as an adjunctive antidepressant treatment for depression by assessing the proportion of patients with MADRS scores ≤10 at Week 4 and Week 8. |
| Secondary efficacy end points | | |
| Clinical symptoms improvement | Reduction rates in MADRS and QIDS-SR16 scores at each visit. | To evaluate the efficacy of perospirone as an adjunctive antidepressant treatment for depression in improving depressive symptoms by comparing the reduction rates of MADRS and QIDS-SR16 scores at each follow-up visit. |
| Reduction rates in HAMA and GAD-7 scores at each visit. | To evaluate the efficacy of perospirone as an adjunctive antidepressant treatment for depression in improving anxiety symptoms by comparing the reduction rates of HAMA and GAD-7 scores at each follow-up visit. |
| Reduction rates in PSQI scores at each visit. | To evaluate the efficacy of perospirone as an adjunctive antidepressant treatment for depression in improving sleep quality by assessing the reduction rates of PSQI at each follow-up visit. |
| Reduction rates in SHAPS scores at each visit. | To evaluate the efficacy of perospirone as an adjunctive antidepressant treatment for depression in improving the symptoms of anhedonia by comparing the change rates of SHAPS scores at each follow-up visit. |
| Reduction rates in CGI and BSI  -CV scores at each visit. | To evaluate the efficacy of perospirone as an adjunctive antidepressant treatment for depression in alleviating symptoms of suicidal ideation and improving overall clinical impression by comparing the change rates of CGI and BSI-CV subscale scores at each follow-up visit. |
| Quality of life and social functionings | Change rates in SDS and Q-LES-Q-SF scores at each visit | To evaluate the efficacy of perospirone as an adjunctive antidepressant treatment for depression in improving patients’ quality of life and social functionings by comparing the change rates of SDS and Q-LES-Q-SF scores at each follow-up visit. |

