| Cognitive performance | Change rates in neurocognitive test scores (including Digit Span Test, Stroop Color Word Test, Trail Making Test, Hopkins Verbal Learning Test, and Digit-Symbol Substitution Test) and Self-Rating Questionnaire for Cognitive Dysfunction-Depression (PDQ-D) Score before and after treatment. | To evaluate the efficacy of perospirone as an adjunctive antidepressant treatment for depression in improving patients’ cognitive performance by comparing the change rates of each neurocognitive test scores at each follow-up visit. |
| Safety endpoints | | |
| Safety | TESS scores | To evaluate the safety of perospirone as an adjunctive antidepressant treatment for patients with MDD when used in combination with antidepressants, utilizing the TESS to assess the severity of AEs and the measures taken for their management. |
|  | Incidence of AEs | To evaluate the safety of perospirone as an adjunctive antidepressant treatment for patients with MDD when used in combination with antidepressants, based on the incidence of AEs during treatment. This assessment includes the overall incidence of AEs, the incidence of extrapyramidal symptoms (EPS), liver and kidney function, and ECG abnormalities. |

1. Study Design

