## Efficacy assessments

### 8.1.1 Primary efficacy assessments

- **MADRS response rate**: the proportion of participants with a ≥50% reduction in the MADRS score from baseline at week 4 and week 8.
- **MADRS remission rate**: The proportion of participants with an MADRS score ≤10 at week 4 and week 8.

This study evaluates the efficacy of perospirone as an adjunctive antidepressant treatment for MDD by comparing the response rates and remission rates between the study group and the control group.

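### Section 8.4.1 exempts undefined endpoint events from the AE definition, although the trial has no event to which this fits; under a broad reading it conflicts with section 8.4.6 and can thin out AE and SAE counts

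*Protocol*

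**What the plan says.** Section 8.4.1 opens with a broad definition: an AE is any untoward medical occurrence during the study, whether or not the drug caused it. A carve-out follows: "Endpoint events are not considered AEs unless" the investigator, using clinical judgement on the course, severity or other features of the case, decides that it should be treated as an exception. The next paragraph says "Any AE, regardless of its severity or whether it is related to the study medication, should be recorded in the CRF".

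The protocol does not define an endpoint event. Its endpoints are:

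- **Primary efficacy:** MADRS response, described in section 8.1.1 as "the proportion of participants with a ≥50% reduction in the MADRS score from baseline at week 4 and week 8", and MADRS remission. Section 12, item 4, later makes week 8 primary and week 4 secondary.
- **Secondary efficacy:** scale changes, among them "Change rates in each Clinical Global Impression (CGI) and Beck Suicidal Ideation Scale (BSI-CV) subscales scores at each visit" (synopsis, section 1.1). The table in section 3 gives their purpose as showing efficacy "in alleviating symptoms of suicidal ideation and improving overall clinical impression".
- **Safety:** TESS and "Incidence of adverse events" (synopsis). The section 3 table says that safety is judged "based on the incidence of AEs during treatment".

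Four other places bear on the point. Section 8.4.6 treats conditions present at screening as baseline but requires an AE record if the participant gets worse at any time. Section 8.4.2 defines an SAE as an adverse event that meets one of six criteria. Section 8.4.8 asks for SAEs to reach the sponsor immediately, usually within 24 hours. Section 8.4.10, on events of special interest, is marked not applicable.

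**The concern.** An endpoint-event exemption makes sense where the efficacy endpoint is itself a harmful clinical event that is counted elsewhere. Here the efficacy endpoints are favourable outcomes or scale scores, so the sentence has no natural object. Each site has to decide what it covers.

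The nearest candidates are the domains that the efficacy scales measure: depression severity (MADRS, CGI) and suicidal ideation (BSI-CV). These are also domains in which harm matters in an 8-week add-on trial of patients with MDD. Exclusion criterion 2 keeps out people with serious suicidal ideation or attempts, so ideation that emerges on treatment is informative about safety. If some of the 10 centres in section 12 record such cases as AEs and others leave them to the rating scales, the AE and SAE comparison between arms rests on an uneven numerator, and some serious cases may never enter the SAE reporting route.

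**Working it through.** No planned figure depends on this sentence, so there is nothing to recompute. The check sets the rules side by side.

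**Step 1: Does anything fit the term?** MADRS response and remission are good outcomes and could not be AEs. Changes in MADRS, CGI, BSI-CV and the other scales are scores, not events. AE incidence is a rate in a treatment group. No relapse, deterioration, suicide attempt or other harmful event is defined as an endpoint. Read narrowly, the sentence covers nothing.

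**Step 2: What follows under each reading?**

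| Occurrence | AE definition, 8.4.1 | Exemption, narrow reading | Exemption, by endpoint domain | Worsening rule, 8.4.6 |
|---|---|---|---|---|
| Depression worsens | AE | No effect, AE | Not an AE unless the investigator makes an exception | AE |
| Suicidal ideation emerges, none at screening | AE | No effect, AE | Not an AE unless the investigator makes an exception | Not named; reached only if counted as worsening of the depression |
| Suicide attempt | AE | No effect, AE | Exempt only by stretching the term further, since no act is an endpoint | Not named |

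For worsening depression, the domain reading contradicts both the AE definition and section 8.4.6. For newly emergent ideation it contradicts the AE definition, and section 8.4.6 gives less direct protection because it speaks of conditions present at screening.

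**Step 3: Does AE status carry through?** Section 8.4.2 makes SAEs a subset of AEs, so an event ruled out as an AE is also outside the SAE definition and the section 8.4.8 report. Section 8.2 uses participants with AEs as the numerator of AE incidence. Section 12, item 5, compares AEs, SAEs and AEs leading to discontinuation by chi-square or Fisher tests. Section 7.2 lists disease progression separately from a clinical AE as a reason for withdrawal, so classification can also affect the discontinuation comparison.

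**Step 4: Is there a backstop?** No event of special interest is named. The unanticipated-problem route in section 8.5.1 requires the event to be unexpected for the population studied, which worsening in MDD may not be. BSI-CV is rated at every visit, but the mixed-model paragraph in section 12, item 5, lists only MADRS, QIDS-SR16, HAMA and Q-LES-Q-SF. Group mean changes would not show individual emergent cases in any event.

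**Step 5: Scale per case.** The safety set sizes are not given. Assume that all randomised patients were dosed (108 perospirone, 102 placebo, from the synopsis). One participant whose only AE is such an event then changes overall AE incidence by 1/108 = 0.93 percentage points in the perospirone arm, or 1/102 = 0.98 in the placebo arm. The number of such participants cannot be derived from the document.

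**The case against.** The strongest reply is that the sentence is idle. If no endpoint is an adverse event, the exemption removes nothing, and section 8.4.6 already requires worsening to be recorded without appeal to judgement. The exemption is also only a default: its own wording lets course and severity bring an event back, and serious suicidality is the kind of case that this would reach. The scales are still collected, withdrawals for progression must be documented, and the TESS comparison in section 9.2.3 counts any item above zero without passing through section 8.4.1.

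Much of this stands, and it rules out three stronger readings that a reader might draw.

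- **That the rule removes suicidality and worsening from safety reporting outright.** It does not. There is an investigator exception, section 8.4.6 points the other way for worsening, and the suicidality endpoint is a BSI-CV score change, not a suicidal event.
- **That AEs, being an endpoint, are literally not AEs.** The endpoint is a group-level incidence, and sections 8.4.1 to 8.4.8 plainly require AE recording. The circularity shows that the sentence fits badly, not that AE recording is abolished.
- **That the sentence contradicts the recording paragraph directly after it.** One limits what counts as an AE and the other says that every AE is recorded. The two are compatible. The conflict is with the opening definition and with section 8.4.6.

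The reply does not remove the defect. An idle clause in a definition still invites a site to find a use for it, and the most obvious use conflicts with another section. The protocol does not list the TESS items, so it cannot be relied on to capture suicidality. An exception that rests on individual judgement can also be applied differently across centres.

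**Conclusion.** The concern holds in limited form. Section 8.4.1 contains a default exclusion that is undefined, fits no event in this trial and, if read by endpoint domain, conflicts with the AE definition beside it and with section 8.4.6 on worsening. Because SAE status depends on AE status and no special-interest route exists, a site that reads it this way could leave worsening depression or emergent suicidal ideation out of the AE and SAE comparison and the 24-hour report.

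The size is unknown. The document gives no count of affected events and does not show how sites read the sentence. The conclusion assumes that at least some site could take the broad reading; under the narrow one nothing is lost. Nothing here shows that any event was in fact missed. The point deserves correction because the sentence serves no purpose in this trial and sits in the definition on which every AE and SAE count depends.

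**What to change.** Delete the endpoint-event sentence from section 8.4.1 so that it agrees with section 8.4.6. Add one sentence: emergent or worsening suicidality and worsening depression are recorded as AEs, and as SAEs when a criterion in section 8.4.2 is met, in addition to being rated on BSI-CV or MADRS.

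The synopsis and section 12 describe a trial already carried out, so new wording alone cannot change what was recorded. The report should also say how the sentence was applied at the sites. A practical way is to check BSI-CV and MADRS deteriorations, and withdrawals for disease progression, against the AE and SAE records, and to list any that were not recorded.

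The cost is a small change of wording and one listing. The AE count may rise, by an amount that cannot be foreseen from the document.

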**Note:**

- Medical History includes current illness, past medical history, personal history, marital and reproductive history, menstrual history, and family history.
- Safety Assessments include vital signs, physical examination, complete blood count, blood glucose, blood lipids, liver and kidney function tests, urinalysis, and ECG.
- Specific examination items are detailed in the study schedule.
- Adverse events must be promptly recorded and assessed for their relationship with the treatment using perospirone tablets. Those assessed as definitely related, possibly related, or probably related are considered drug-related adverse reactions.

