## Termination of study intervention

If intolerable AEs occur in participants, or if AEs that the investigator deems may increase the risk to participants are observed, the use of investigational medication should be discontinued. The reasons and timing for the discontinuation of the intervention should be documented in detail.

Discontinuation of the study intervention does not mean discontinuation of the study itself. Participants should continue to follow the procedures outlined in the study protocol. If clinically significant changes in the laboratory tests occur after enrollment (including but not limited to deviations from baseline levels), the investigator or a qualified designated person will determine whether changes in participant management are necessary. Any new clinically relevant findings will be reported as AEs.

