### Requirements for AE recording and follow-up

When participants receiving medical services during visits or monitors conducting reviews, the occurrence of AEs or SAEs should draw the attention of researchers.

All AEs that do not meet the criteria for SAEs will be recorded in the CRF, including both local and systemic reactions. Information to be collected includes a description of the event, onset time, assessment of severity by a physician, relationship to the investigational medication (which can only be assessed by trained personnel with diagnostic authority), and the time when the event is resolved or stabilized. All AEs occurring during the study must be comprehensively documented, regardless of their relationship to the study intervention. All AEs should be followed up until reasonably resolved.

Medical conditions at the time of participant screening should be considered baseline and not reported as AEs. However, if the participant's condition worsens at any time, it should be recorded as an AE.

Changes in the severity of AEs should be documented to assess the duration of the event at different severity levels. Intermittent AEs require recording of onset time and the duration of each onset.

From the time of signing the informed consent form to the end of the trial, investigators should record all AEs/SAEs. At each visit, researchers should inquire about AEs/SAEs that occurred since the last visit and follow up on the outcome of the events until they are resolved or stabilized.

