### AE reporting

Investigators should inform participants to truthfully report any changes in their condition following medication use. Physicians should avoid leading questions. While observing treatment efficacy, attention should also be paid to AEs or unexpected toxic side effects (including symptoms, signs, and laboratory test results). Investigators should analyze the causes, make judgments, and calculate the incidence of AEs.

For AEs occurring during the study, symptoms, severity, onset time, duration, management measures, and course of the event should be documented in the CRF. The relationship between the AEs and the investigational medication should be evaluated, and the form should be signed by the investigator with the date noted.

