### Safety end points analyses

The safety set (SS), included of individuals who have received at least one dose of the randomized investigational drug, were employed to analyze the safety and tolerability profile of the medication by comparing the self-reported AEs/SAEs of the two groups of patients. Since the AEs covered by the TESS involve multiple systems, which could assess the safety of the drug in a more comprehensive manner. Therefore, the TESS was also used for safety evaluation. Nevertheless, since the TESS set to be completed by patients during follow-up visits, on the basis of the SS sample, those with at least one follow-up visit were included for inter-group comparisons of the incidence of AEs based on the TESS. For TESS items, a score of 0 indicates that the patient did not experience the corresponding AE. Conversely, any score greater than 0 signified that the patient experienced the AE during the treatment period.

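### Section 8.4.1 makes the recording of laboratory, vital-sign and ECG abnormalities as AEs depend on relatedness to the drug, against the protocol's own causality-free AE rule, so AE incidence can be under-counted

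*Protocol*

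**What the plan says.** Section 8.4.1 opens with a definition of an AE that applies "regardless of whether there is a causal relationship with the study medication or treatment process". It goes on to require that any AE, of whatever severity and whether or not related to the drug, be entered in the CRF. The last paragraph of the same section treats test findings separately: "Laboratory test results, vital signs, or ECG abnormalities will be recorded as AEs if they are medically related to the study medication". It illustrates the condition as follows: "such as when accompanied by clinical symptoms, necessitating symptomatic treatment, leading to discontinuation of the medication, or resulting in serious consequences".

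Other sections carry no relatedness condition:
- Section 8.4.6: "All AEs occurring during the study must be comprehensively documented, regardless of their relationship to the study intervention".
- Section 7.1, in the paragraph on laboratory changes after enrolment: "Any new clinically relevant findings will be reported as AEs".
- The note to the flowchart in section 1.2 puts recording and the judgement of relationship side by side, without making one depend on the other: "Adverse events must be promptly recorded and assessed for their relationship with the treatment using perospirone tablets".

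Sections 3 and 8.2 place ECG abnormalities within the AE-incidence safety endpoint. Section 8.2 separately compares the proportion of abnormal results between groups for vital signs and laboratory parameters. Footnote h to the schedule in section 1.3 has heart rate and QTc recorded at each visit.

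**The concern.** A blinded randomised comparison of AE incidence works because events are counted first and attribution follows. The difference between arms then shows what the drug does, and individual judgements of cause are secondary. If an investigator must first decide that an abnormality is related before recording it, abnormalities judged unrelated are missing from the count before the arms are compared.

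The endpoint at stake is a named one. ECG findings matter in this trial: section 5.2 excludes patients on QTc, and an ECG is done at every visit. The separate comparison of abnormal results in 8.2 would catch laboratory and vital-sign abnormalities whether or not they became AEs, but the text does not make clear that it covers ECG.

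**Working it through.** The protocol states no figure for this point, so the check is a comparison of texts, followed by a look at whether any size can be derived.

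**1. The recording rules side by side**

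| Place | Applies to | Relatedness needed to record? |
| --- | --- | --- |
| 8.4.1, definition | all AEs | no |
| 8.4.1, CRF recording | all AEs | no |
| 8.4.6 | all AEs | no |
| 7.1 | new clinically relevant findings | no |
| 8.4.1, last paragraph | laboratory, vital-sign and ECG abnormalities | yes, as worded |

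The last row conflicts with the others. This is current text, and the adjustments in section 12 do not touch AE recording.

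**2. The condition against its own examples.** The four examples are symptoms, need for treatment, stopping the drug and serious consequences. Each is a test of clinical significance. None is a test of cause, and section 8.4.5 has its own causality criteria (timing, dechallenge, rechallenge, alternative explanation). So the condition and its illustration point in different directions.

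**3. The condition against the grading scale.** Grade 1 in section 8.4.3 includes findings without symptoms that only a test detects and that need no intervention. Such a finding can be graded as an AE, but it resembles none of the four examples. Two sites could both follow the protocol and treat the same QTc finding differently.

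**4. Whether ECG has a route that does not depend on AE status.** Section 8.3 lists ECG among the laboratory tests at baseline and at Visits 1, 2 and 3. On that usage the abnormal-proportion comparison in 8.2 covers it, and so does the normal/abnormal table in 9.2.4, item 3. But 8.4.1 names ECG apart from laboratory results, 8.2 names ECG abnormalities separately, and the list of safety indicators in 8.2 leaves ECG out. Coverage is ambiguous.

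**5. Whether a size follows.** Let the placebo rate of an abnormality be b and the perospirone rate b + e, where e is the excess caused by the drug. Suppose a share k of background events and a share m of excess events are recorded, equally in both arms. The recorded rates are kb + me and kb, so:
- recorded risk difference = (kb + me) − kb = me;
- recorded risk ratio = 1 + (m/k)(e/b).

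If recording is thinned evenly (k = m = s), the difference shrinks to s times its true value and the ratio is unchanged. If background events are lost but the excess is kept (k < 1, m = 1), the difference is unchanged and the ratio rises. The protocol gives none of b, e, k or m. The number of recorded events falls in both cases, but neither the amount nor the effect on the comparison can be stated.

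**The case against.** The strongest reply is that this is a slip of wording or translation. The sentence says 'if' and does not say 'only if', the examples show that clinical significance was meant, and 8.4.6 and 7.1 would bring a clinically relevant finding into the record anyway. The intended meaning is probably just that. Even so, a recording rule introduced by 'if' is naturally read as a condition, and the condition written down is relatedness. Reading the intent from the examples supports correcting the sentence.

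The second reply is that other comparisons exist: TESS, overall AE rates, and the abnormal-result comparisons in 8.2 and 9.2.4, which may already include ECG because 8.3 calls it a laboratory test. This stands in part. A reader might infer that ECG abnormalities would not be compared at all. The protocol does not support that; coverage is unclear, which is a smaller fault.

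A reader might also infer that the rule biases the comparison between arms or costs power to detect a cardiac signal. Neither is shown. Section 4.5 keeps physicians and assessors blind to allocation, and step 5 of the working shows that the effect depends on which events are lost. A relatedness filter could remove background events more readily than drug-caused ones, so even the direction of any change in power is open.

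Finally, section 9.2.3 describes the AE analysis as "comparing the self-reported AEs/SAEs of the two groups of patients", although investigators record AEs under 8.4.1 and 8.4.6. A reader might take this to exclude events found by investigators. Section 12, item 5 compares overall AE and SAE rates with no such limit, so this is a minor matter of wording.

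**Conclusion.** The point holds as an internal contradiction in the AE recording rule. The last paragraph of 8.4.1 makes relatedness a condition for recording laboratory, vital-sign and ECG abnormalities, while the rest of 8.4.1, 8.4.6 and 7.1 do not. Followed literally, it leaves clinically significant abnormalities judged unrelated out of the AE incidence, including the ECG component named in sections 3 and 8.2.

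The consequence is a possible under-count of unknown size. It rests on one assumption, that at least some sites applied the sentence as written. No bias between arms, loss of power or missing comparison is established.

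**What to change.** 1. **Section 8.4.1.** Replace the relatedness condition in the last paragraph with: *if they are clinically significant, regardless of relationship to the study medication*. Keep the four examples, which then fit. Grade relatedness afterwards under 8.4.5.
2. **Section 8.2.** Name ECG, including QTc, beside vital signs and laboratory parameters in the comparison of abnormal proportions. This is needed as well as the first change, because a silent QTc abnormality may not count as clinically significant and so may never become an AE.
3. **Section 9.2.3 (minor).** Refer to all recorded AEs and SAEs in place of self-reported ones, to agree with 8.4.1, 8.4.6 and section 12.

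The cost is a few more recorded AEs and one more table line. The synopsis already reports final enrolment of 210 (108 and 102), so the first change cannot recover AEs that were never recorded. The second can still be carried out on the QTc values recorded at each visit.
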